**Fig. 2 Fig2:**
[figure not shown]
Overview of the subprojects and their role in the FACE project

### Participants

The target population are 5000 young adults from the general population. Inclusion criteria are an age between 18 and 21 at baseline and the provision of an informed consent. Exclusion criteria are insufficient mastery of the German language, a cognitive or physical inability to take part in the online questionnaire reported by a relative, for example reported by a relative, or the inability to follow the studies procedures, e.g., due to not having internet access.

Addresses of 15,000 young adults are provided by the Swiss Federal Office of Statistics. Participants are drawn at random from all individuals living in a private household in German-Speaking municipalities that did not already participate recently in another survey. We will send an invitation letter with the study information to all young adults by postal mail. The invitation letter also lists psychosocial services and helplines and a small giveaway in form of summer flower seeds. Participants have also the chance to take part in a participation-associated lottery with monetary winnings. For the first wave, participants can win 200 vouchers for a Swiss Supermarket chain for 50 CHF (approximately 55 US Dollars). For each of the next waves, they can win 75 vouchers for 50 CHF. Such incentives have been shown to increase response rates [45, 46]. The invitation letter contains an identification number and a link to the study webpage. Using their unique 6-digit identification number, participants can give their written informed consent electronically on REDCap [47, 48] by signing with their mouse or touch screen before starting to fill out the online questionnaires.

We expect a response rate of 30%. If the targeted sample size will not be reached, a second sample will be recruited via educational facilities such as universities, teacher training colleges or military training schools. A link to the study website with the full study information and the informed consent will either be posted on university webpages and other billboards or forwarded via intermediary student organisations. Invitations for follow-ups will be sent to the e-mail address provided by participants in the baseline questionnaire. For the follow-ups, two reminders per e-mail are planned for participants not replying to the invitation.

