### The present study

The present study aims to overcome several shortcomings of previous studies and theoretical models: Firstly, while most theoretical models and empirical studies have focused either on emotion regulation or social information processing, the FACE study combines these two strands of research and investigates the longitudinal interplay and relative strength of emotion regulation and social information processing as mediators for the link of ACE and psychosocial functioning. This is relevant, as the intensity of emotions and emotion regulation may affect different social information processing tasks. Lemerise and Arsenio’s Integrated Model of Emotion Processes and Cognition in Social Information Processing [39] posits that a database of memories, social schemas, social knowledge and acquired rules as well as the intensity of emotions, emotional processing and emotion regulation affect all stages of social information processing, including the perception and encoding of cues, their interpretation, the clarifications of goals, and finally the behavioural response. These factors may affect good social relationships and seeking and receiving social support.

Secondly, while many previous studies ignore the subtypes of ACE as potential moderators for differential health outcomes and employ a single risk or a cumulative risk approach, the FACE epidemiological study uses comprehensive measures for assessing distinct patterns of ACE. This may provide a better understanding of more complex risk environments [40]. Such patterns could then be related to patterns of psychosocial adaptation, such as vulnerable, resilient or average psychosocial functioning. Complementary to this categorical approach, we will investigate a dimensional approach to vulnerability and resilience which defines resilience as “doing better than expected” compared to individuals with similar levels of adversity [41, 42].

Thirdly, the FACE epidemiological study uses a longitudinal design complemented by an ecological momentary assessment in a large population-based sample which can disentangle the short- and long-term temporal interplay of emotion regulation and social information processing. It thus provides a better understanding of the mechanisms underlying the association between ACE and psychosocial functioning.

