## Discussion

Adverse childhood experiences have a high prevalence, cause considerable personal suffering and are a well-established transdiagnostic risk factor for various mental and physical health conditions throughout life. However, less is known about the processes through which ACE are linked to multiple negative outcomes. A better understanding of the underlying processes is crucial for an improved insight into risk and resilience processes and for tailoring interventions.

The main aims of the FACE epidemiological study are to investigate the associations between ACE and psychological functioning and to investigate to which degree these associations are mediated by deficits in emotion regulation, social information processing and lower social support. It is the first study that links two strands of theory and research, i.e., emotion regulation and social information processing in the context of ACE, and analyses the short- and long-term longitudinal interplay of ACE, emotion regulation, social information processing, social support and psychosocial functioning. The results will substantiate the Integrative Model of Emotion Regulation and Social Information Processing in the Aftermath of ACE. The longitudinal design with a large sample size will provide an opportunity to provide new insights into causal mechanisms linking ACE to psychosocial functioning and to test moderating effects of several other factors such as gender or socioeconomic factors. With its large sample size, the study will allow to identify different patterns of ACE, providing new insights into how ACE co-occur and how these patterns are related to distinct trajectories of psychosocial functioning.

Furthermore, the FACE epidemiological study provides data on self-reported ACE as well as service use among young adults to inform healthcare policies and the provision of appropriate healthcare services. It prospectively identifies factors that facilitate or hinder service use in general and the use of the FACE self-help programme specifically. The FACE project examines which young adults are especially receptive to an intervention –and the age at which they would be most receptive—as well as seeking to identify the developmental stage (regarding life transitions) at which the intervention is most effective. The combined data of both subprojects provide the empirical basis to advance theory-driven models of enrolment and engagement with m-health interventions.

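### On the article's own figures the second sample from educational facilities is the expected case, yet it counts toward one 5,000 described as a population-based sample

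*Protocol article*

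**What the plan says.** Under Participants, the article sets the goal: "The target population are 5000 young adults from the general population". The primary source is a register sample: "Addresses of 15,000 young adults are provided by the Swiss Federal Office of Statistics", and "Participants are drawn at random from all individuals living in a private household in German-Speaking municipalities". On yield it says "We expect a response rate of 30" per cent.

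The fallback applies only if the target is missed: "a second sample will be recruited via educational facilities such as universities, teacher training colleges or military training schools". These people are reached through a study link placed on university sites and notice boards or passed on by student bodies. The stated inclusion criteria are age 18 to 21 and consent. The register draw's limits on household type and municipality are not repeated for this group.

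The Abstract describes the study as a large population sample. Under The present study, the longitudinal design is said to operate "in a large population-based sample which can disentangle the short- and long-term temporal interplay". The Discussion adds that the study "provides data on self-reported ACE as well as service use among young adults to inform healthcare policies".

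The Statistical analysis section sizes everything on a single 5,000: 25% (1,250) with ACE, and about 3,000 left at wave 4. It describes latent class and profile analyses, structural equation models, growth models and logistic regressions without distinguishing the two sources. The predictors listed for the logistic models are ACE, age, gender, socio-economic status and psychosocial functioning.

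**The concern.** The two samples differ in kind. The first is a random draw from a defined frame. The second is self-selected, has no known selection probability, and comes from settings defined by education or military training. If those settings differ from the general population in ACE, functioning or service use, a combined figure is a blend whose mix depends on how far register recruitment fell short. The article gives no data on such differences, so their size is an assumption here.

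The wording of the condition makes the second sample look like a contingency. If the article's own numbers already trigger it, the sample obtained by following the plan does not have the property claimed for it. ACE and service-use frequencies offered to policy makers are the most exposed, together with the class and profile proportions, which depend directly on who is sampled.

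**Working it through.** **Inputs from the article.** 15,000 addresses, 30% expected response and a target of 5,000 (Participants); 25% expected to report ACE (Statistical analysis, justification of sample size).

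**Step 1: does the stated yield reach the target?** 15,000 × 0.30 = 4,500, so the target is not reproduced. The shortfall is 5,000 − 4,500 = 500, and 500 / 5,000 = 10%. Reaching 5,000 from the register alone needs 5,000 / 15,000 = 33.3% response.

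If the response probability were exactly 30%, the standard deviation of the number of responders would be √(15,000 × 0.30 × 0.70) = 56.1, and the target would lie 500 / 56.1 = 8.9 standard deviations above expectation. Only a response rate above the one planned for avoids the second sample.

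**Step 2: share of the second sample, and shift in a pooled prevalence.**

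- Share = (5,000 − 15,000 × response) / 5,000.
- Shift = share × (prevalence in second sample − prevalence in register sample).
- Assumptions: register prevalence equals the article's 25%; the second sample differs by 5 or 10 points in either direction; response rates below 30% are hypothetical.

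| Response | Register n | Second sample n | Share | Shift, 5-point difference | Shift, 10-point difference | Pooled prevalence, ±10 points |
|---|---|---|---|---|---|---|
| 30% (stated) | 4,500 | 500 | 10% | 0.5 | 1.0 | 24 to 26% |
| 25% (assumed) | 3,750 | 1,250 | 25% | 1.25 | 2.5 | 22.5 to 27.5% |
| 20% (assumed) | 3,000 | 2,000 | 40% | 2.0 | 4.0 | 21 to 29% |

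**Step 3: compare with sampling error.** At 25% prevalence and n = 5,000 the standard error is √(0.25 × 0.75 / 5,000) = 0.0061, so the 95% half-width is 1.96 × 0.0061 = 1.2 points. At the stated response rate even the 10-point difference (1.0) stays inside that. At 25% and 20% response a 10-point difference exceeds it. A shift of this kind does not shrink as n grows.

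**Step 4: precision lost by using the register sample alone.** At n = 4,500 the half-width is 1.96 × √(0.25 × 0.75 / 4,500) = 1.3 points, against 1.2 at 5,000.

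**The case against.** The strongest reply is that this is a condensed article. Source terms, weights, register-only runs and duplicate checks are commonly left to an analysis plan, which is not shown. That stands: their absence is not the point here. What remains is a conflict within the article between its recruitment figures and its description of the sample.

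Second, the article never says that the two samples will be analysed as one without distinction. A reader might infer that, but pooling is only implied, by the shared target and the lack of any separate handling. The label is also attached to the sample in a design description and not to results.

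Third, the study is mainly about associations, mediation, adaptation patterns and predictors of service use. ACE prevalence is not a listed objective; the policy use appears in the Discussion. A reader might infer that the main hypotheses are compromised, but nothing here shows that, and the logistic models already include socio-economic status.

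Fourth, the Discussion does name non-response bias. With 70% non-response, its bias is 0.70 × the difference between responders and non-responders: 1.4, 3.5 or 7.0 points for an assumed 2, 5 or 10. At 30% response that can outweigh the second sample's effect. But the acknowledgement does not mention mixed recruitment.

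Other tempting inferences also go too far. The article does not say how second-sample participants are identified, so double entry is possible but not shown. It mentions addresses only, so frame variables suitable for calibration weights cannot be presumed.

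**Conclusion.** The point holds as an internal inconsistency with a limited effect. The 4,500 against 5,000 is the article's own arithmetic and needs no assumption. It makes the second sample the expected case, at about 10% of participants, so the 5,000 as planned is a mixed sample and not a population-based one throughout.

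At the stated response rate the consequence for a prevalence is modest: up to 1.0 point under an assumed 10-point difference, within sampling error. It becomes material, at 2.5 to 4.0 points, only if response falls to an assumed 25% or 20% and the same difference holds. Class and profile proportions are exposed in the same way, but the article offers nothing from which to quantify that. The documents do not support the stronger reading that associations and mediation are invalidated.

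**What to change.** - Under Participants, state the expected register yield as about 4,500, or note that 5,000 needs a 33.3% response, and describe the second sample as expected.
- Record recruitment source for every participant from the start, since it may not be recoverable later.
- Report ACE and service-use frequencies from the register sample.
- Repeat the main structural equation, latent class and profile, and growth models in the register sample as a sensitivity analysis.
- Keep the population-based label for register-sample results. Add non-response weighting only if suitable frame variables are actually held.

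Forcing source into every model as a covariate is not recommended. ACE precede age 18, and being in a university or military school at 18 to 21 comes later, so that adjustment could condition on a consequence of the exposure.

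The cost is one indicator variable, some extra model runs, and slightly wider descriptive intervals from using about 4,500 instead of 5,000. The second sample can still serve the pooled models and recruitment to the intervention study, which is what the 5,000 was sized for.

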### Measures

Measures used in the study are presented in Table 1. Apart from adverse childhood experiences and some socio-demographic variables, all measures will be assessed at baseline and at the three follow-up waves. Wherever possible, we used validated translations. Measures that were not available in German were translated by multiple team members into German. Differences in translations were resolved by discussion. The translations were also double checked for comprehensibility by university students who are close to the age range of the target population.

**Table 1 Tab1:** Overview of the measures

Childhood experiences (only at t1), main exposure variable	
Adverse childhood experiences	- Child Maltreatment. Childhood Trauma Questionnaire, 5 subscales (physical and emotional neglect and abuse, sexual abuse), 5 items each [49, 50]. To assess the timing and chronicity of ACE, all participants reaching the subscale threshold for slight to moderate maltreatment were additionally asked in which years of their life this subtype of maltreatment occurred. - Witnessing violence to other family members (5 items); verbal and physical abuse by peers (6 items). Items were adapted from the German version of the Maltreatment and Abuse Chronology of Exposure’(MACE) scale [51, 52]. Additional item were added for the timing and chronicity per scale.
Family context and relationships	- Family Context before age 18, 3 items. Adapted from the C-SURF study [53]. - Satisfaction with family relationships before age 18: mother, father, and siblings. Adapted from the C-SURF study [53]. - Psychiatric problems of parents and siblings, Adapted from the C-SURF study [53].
**Psychosocial functioning**	
Well-being	- Ryff’s Psychological Well-Being Scale, 42 items, 7 for each dimension (autonomy, environmental mastery, personal growth, positive relations with others, purpose in life, and self-acceptance) [54, 55], German translation adapted from Staudinger (1990) [56].
Life satisfaction	- Diener Satisfaction with life scale [57], 5 items. German version [58]. - Additional questions about satisfaction with different types of relationships: to friends, to romantic partner, to parents and to family/relatives.
Work and social adjustment	- Work and Social Adjustment Scale, 5 items [59].
Psychosocial and somatic problems and distress	- Brief Symptom Inventory (BSI-18) assessing symptoms of somatisation, depression and anxiety [60]. - Externalising Problem Screener, 10 items [61]. - Psychosocial distress in 13 different areas of life, for example school/work, sleep, romantic relationship, physical health, financial situation, adapted from Brodbeck (2007) [62]. - Diagnosis of COVID and Long COVID, worsening of psychological distress due to COVID-19. - RIWA Critical Life Events, 21 items, adapted from Brodbeck (2007) [62]. - Suicidal ideation and attempts, 2 items from the Suicidal Behaviours Questionnaire-Revised [63, 64]. On this page, a phone number and webpage in case of need for help is indicated.
Substance use	- Frequency of use for tobacco, alcohol, cannabis, party drugs, cocaine/heroin, other drugs, and pharmaceutical drugs for non-medical use. - For substance used: age at first use and the 4-item Addiction Screener [65].

Secondary outcomes and potential mediators for the association between ACE and primary outcomes	
**Emotion regulation**	
Emotional reactivity	- Emotion Reactivity Scale, 21 items [66].
Perseverative thinking	- Perseverative Thinking Questionnaire, 15 items [67].
Self-efficacy for managing emotions	- PROMIS Short Form v1.0—Self-Efficacy for Managing Emotions, 7 items [68].
**Social information processing**	
Rejection sensitivity	- Rejection Sensitivity Questionnaire, 9 scenarios with 2 questions each [69, 70].
Interpretation bias	- WSAP-hostility scale for hostile interpretation bias, 16 items with 2 questions each [71]. - Interpretation bias index for PTSD, 13 items [72].
Social understanding	- Tromsoe Social Intelligence Test: Social awareness & social information processing, 14 items [73].
**Social and professional support**	
Social support	- Social Support Questionnaire, short Version, (F-SozU K-14), 14 items [74] plus one item on informational support.
Professional support and service use	- Use of child and youth counselling services, ambulant and residential psychological and psychiatric treatment as well as child protection services, 5 items (partially only at t1).

### Statistical analysis

Significance level will be two-sided α = 0.05. Due to the large sample size, effect sizes will be prioritised over the significance level for the interpretation of the results. Cohort data will be analysed with a range of observed and latent variable models using Mplus that include person- and variable-centred approaches. Distinct patterns of ACE will be identified using a Latent Class Analysis based on the subtype and frequency of childhood experiences, for example patterns combining subtypes of child maltreatment, household dysfunctions or bullying by peers. Psychosocial functioning as primary outcome will be analysed in a variable- and a person-centered approach. For the variable-centered approach, a composite measure of psychosocial functioning will be computed using Factor Analyses including bifactor models. For the person-centered analyses, a Latent Profile Analysis is used to identify psychosocial adaption patterns, for example an average group, a resilient group, a moderately vulnerable group, and a highly vulnerable group.

The main hypotheses for the associations between childhood experiences, emotion regulation, social information processing and psychosocial functioning will be analysed using structural equation models with subtypes, dimensions, or patterns of childhood experiences as predictor and moderator variables and psychosocial functioning as outcome variable. (Moderated) mediation hypotheses will be tested using structural equation modelling with the simultaneous inclusion of dimensions of emotion regulation and social information processing variables as mediators linking childhood experiences with psychosocial functioning.

The trajectories of psychosocial adaptation, emotion regulation strategies and social information processing will be investigated with Growth- and Growth-Mixture models. For the longitudinal trajectories of psychosocial functioning across emerging adulthood, we expect to find a chronically dysfunctional group, a recovering group and a resistant trajectory group over time using Latent Growth Mixture Models. The effect of the use of mental health care services after baseline will be analysed with a Latent Transition Analysis where service use will be entered as predictor and the transition between the subgroups as outcome variable.

Logistic regression analyses will be used to analyse predictors of service use and enrolment to the FACE intervention (as binary variables). Predictor variables are simultaneously entered in the model and include ACE, age, gender, socio-economic status and psychosocial functioning.

Where an influence of the COVID-19 pandemic is to be expected, we will adjust for the impact of the crisis on individuals to ensure that trends are not created by the consequences of the COVID-19 epidemic or conduct sensitivity analysis to gauge the effect of the COVID-19 crisis. For example, there may be a general improvement of mental health in case the pandemic is ending between two waves of our study, and it will be important to account for that when considering trends across the four waves.

*Justification of sample size:* The sample size of the epidemiological study is determined with consideration of the number of participants needed in the FACE intervention study, i.e., 350 participants. This sample size allows the detection of small effect sizes for the interaction between time (pre, post, follow-up) and the two treatment condition SSIP vs SER, mediation analyses with parallel mediators in a structural equation modelling framework and, a multi-group model for each treatment arm, and an accurate estimates of the regression coefficients, the variance components and the standard errors for multilevel analyses of the EMA data [75, 76], details will be reported elsewhere]. For the FACE *epidemiological study*, the sample size of 5000 at baseline is based on the expectations that 25% (n = 1250) of the participants report ACE and that a third of them (n = 375) give an informed consent for the intervention study and start the FACE self-help programme.

*Handling of missing data:* An attrition of 40% is expected in the fourth wave of the epidemiological study, resulting in a sample of about 3000 participants at the fourth wave. We will conduct missingness analyses which identify patterns and predictors of missingness and determine whether missing data are completely at random, at random or non-ignorable. If missingness at random is supported, we will use Multiple Imputations in Mplus [77]. Sensitivity analyses will compare the results of different ways of imputing missing data including complete case analyses and if appropriate full information maximum likelihood.

*Data storage:* The electronic consent, the questionnaires and the case report forms are programmed in REDCap. Time, table, data field and altered value, and the person are recorded (audit trail). A role concept with personal passwords (members of the study team, i.e., principal investigator, research associates and assistants) regulates permission for each user to use the system and database as he/she requires. For each data extract, quality checks are carried out, the data is adjusted and made securely available in a coded form. The final data set will be available to interested researchers after the end of data collection in accordance with the funding agency’s open data policy.

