Processes linking ACE with psychosocial functioning may depend on the subtype of ACE. ACE represent distinct experiences such as physical, emotional or sexual abuse, neglect, or household dysfunctions such as parental substance use or psychopathology which can have different consequences on physical and psychological health and psychosocial adaptation. However, different definitions of ACE and the fact that ACE often co-occur [2] hinder the integration of results. The analysis of the effects of ACE traditionally employs a single risk approach, examining only one subtype of ACE and ignoring the high co-occurrence of ACE, or use a cumulative risk approach, summarizing different forms of ACE and not accounting for the fact that ACE represent distinct experiences [10]. A more recent development addressing this issue is the Dimensional Model of Adversity and Psychopathology (DMAP) by McLaughlin, Sheridan and colleagues [10–13] which conceptualises ACE within underlying dimensions of adversities. These dimensions are the level of threat associated with abuse and level of deprivation associated with a lack of cognitive inputs or social stimulation as well as neglect. These dimensions have a differential impact on cognitive and emotional development. The exposure to threat in early life has been linked with higher perceptual sensitivity and attention biases towards negative emotional stimuli and patterns of information processing that prioritise threat-related information, higher emotional reactivity, and poor emotion regulation. Deprivation has been associated with impaired cognitive learning, i.e., in the domain of language and executive functioning.

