## Methods

### Objectives

The primary objective of the study is to examine the impact of self-reported ACE on psychosocial functioning and to investigate the longitudinal interplay and relative strength of emotion regulation and social information processing, as processes and mediators linking ACE with psychosocial functioning in young adults in the framework of the Integrated Model of Emotion Regulation and Social Information Processing in the Aftermath of ACE. A multivariate approach will identify distinct adaptation patterns of psychosocial functioning, such as chronic maladaptive, intermittent maladaptive, resilient and recovery trajectories [43, 44]. The main hypotheses are that ACE are associated with a higher risk for lower psychosocial functioning in young adulthood and that this association is mediated by (a) deficits in emotion regulation, i.e., higher emotional reactivity, more perseverative thinking and lower self-efficacy for managing emotions, and (b) social information processing, i.e., higher rejection sensitivity, higher levels of interpretation biases and lower social understanding. Referring to the DMAP, we expect that emotion regulation shows a stronger indirect effect for the association between the threat dimension of ACE and psychosocial functioning than for the association between the deprivation dimension of ACE and psychosocial functioning. Furthermore, the FACE epidemiological study aims to identify factors that facilitate or hinder the use of mental healthcare services among young adults with history of ACE.

Secondary objectives are to analyse the effects of emotion regulation and social information processing on the quality of friendships and social support; to explore the longitudinal associations of emotion regulation and social information processes on facets of psychosocial functioning and distress and to investigate the longitudinal associations between emotion regulation and social information processing. Additional explorative analyses investigate differential effects of distinct patterns of ACE on emotion regulation and social information processing as well as psychosocial functioning. Figure 1 gives an overview of the assessed variables and the hypothesised associations between them.

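### No cumulative-severity benchmark is stated for the ACE pattern models, so functioning differences between latent classes may reflect the amount of adversity rather than its type

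*Protocol article*

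**What the plan says.** The Background section faults the cumulative-risk approach for "summarizing different forms of ACE and not accounting for the fact that ACE represent distinct experiences" and notes that ACE often occur together. The section on the present study makes the contrast the second of three advances: whereas many earlier studies "employ a single risk or a cumulative risk approach, the FACE epidemiological study uses comprehensive measures for assessing distinct patterns of ACE".

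The Statistical analysis section forms the patterns by a "Latent Class Analysis based on the subtype and frequency of childhood experiences". It tests the main hypotheses with "structural equation models with subtypes, dimensions, or patterns of childhood experiences as predictor and moderator variables". Bifactor models are mentioned there only for the psychosocial-functioning composite, not for the exposure. The same section sets the rule that "effect sizes will be prioritised over the significance level for the interpretation of the results".

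The Objectives section labels the comparison of pattern effects as additional and explorative. One type-specific expectation stands beside the main hypotheses: emotion regulation should show a "stronger indirect effect for the association between the threat dimension of ACE and psychosocial functioning than for the association between the deprivation dimension".

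Overall adversity comes closest to being modelled in two places. The section on the present study describes a dimensional view of resilience, which compares people at similar adversity levels. The logistic regressions for service use and enrolment enter ACE without stating how it is coded. Neither is described as a test of type against amount.

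**The concern.** Subtypes co-occur, and frequency is one of the class indicators. The resulting classes are therefore likely to differ in total adversity as well as in its mix. If functioning falls with total adversity alone, the classes will still differ in functioning. The pattern view and the cumulative view both predict that gap, so the gap cannot decide between them.

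At stake is the second stated advance, the added value of patterns over a cumulative score. Giving effect sizes priority over p-values does not protect against this, because gaps produced by amount alone can be large.

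**Working it through.** The article gives no figure on this point, so there is nothing to reproduce. The check has two parts: a reading of the stated models, and simulations in which type has no effect by construction.

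**1. Stated models.** Exposure in the main models: subtypes, dimensions or patterns. Construction of patterns: latent class analysis (LCA) on subtype and frequency. Comparator or covariate for overall severity: none named.

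**2. Simulation with frequency levels.** Assumed: N = 5000, seven subtype scales at three frequency levels driven by one severity dimension, functioning depending on severity only (r = -0.35), 12 replicates, one to five classes compared by BIC.
- Three classes were chosen in 12 of 12 samples, always ordered by total severity.
- The gap between lowest and highest class was 0.74 to 1.04 SD.
- R-squared was 0.044 to 0.069 for classes alone and 0.051 to 0.074 for the sum score alone.
- Classes added 0.0000 to 0.0025 to a model with the total and its square root.

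**3. Simulation with the article's prevalences.** From the article: N = 5000; emotional abuse 36.3%, physical abuse 22.6%, sexual abuse 12.7%, emotional neglect 18.4%, physical neglect 16.3% (Background); two-sided 5% level. Assumed: standardised severity effect 0.4; five binary subtypes; loadings 0.70 for all (count version) or 0.55 to 0.80 (latent version); three or four classes; modal assignment; 40 data sets per setting. The increment is R-squared(count + classes) minus R-squared(count).

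| Outcome driven by | Classes | Gap, extreme classes (SD) | R² classes | R² count | R² both | Increment | Classes significant alone | Classes significant beside count |
|---|---|---|---|---|---|---|---|---|
| Count | 3 | 1.235 | 0.133 | 0.158 | 0.159 | 0.001 | 100% | 10% |
| Count | 4 | 1.266 | 0.139 | 0.162 | 0.163 | 0.001 | 100% | 0% |
| Latent severity | 3 | 0.906 | 0.082 | 0.092 | 0.095 | 0.003 | 100% | 80% |
| Latent severity | 4 | 0.827 | 0.080 | 0.089 | 0.092 | 0.003 | 100% | 70% |

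With 40 data sets the percentages are coarse: 10% is 4 of 40. In the latent version the subtypes measure severity unequally. A plain count then leaves a small residue that the classes pick up, so it is an imperfect benchmark; a general severity factor would be the fuller one.

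**4. Threat versus deprivation.** In the same data, threat was the count of the three abuse types and deprivation the count of the two neglect types, entered jointly.
- Count version: raw slopes were 0.305 and 0.305 (three-class runs) and 0.314 and 0.303 (four-class runs). Equality was rejected in 2.5% and 5% of data sets, so the test holds its level.
- Count version, standardised slopes: 0.273 against 0.185, and 0.280 against 0.184. Equality was rejected in 92.5% and 97.5%. The ratio 0.273 / 0.185 = 1.48 arises only because the two counts have different standard deviations.
- Latent version, raw slopes: equality was rejected in 72.5% and 70%, because measurement quality is unequal.

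These are total slopes. The article's expectation concerns indirect effects, which were not simulated.

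**The case against.** The strongest reply is that a journal article condenses a fuller plan. It announces a range of models rather than a closed list, and a comparator model could well be in the full document. This stands in part. A reader might infer that the study will never fit a severity model; the article does not support that. The resilience approach implies relating functioning to adversity level, and ACE in the logistic regressions may be a total. What remains is that the article does specify the exposure, in a way that mixes type with amount, and describes no comparison that would separate them.

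A reader might also extend the point to dimensions and subtypes. That is too broad. Entered jointly on a common scale, they contain the cumulative model as the equal-slopes case, and part 4 shows that the equality test on raw slopes then works when the count drives the outcome. Trouble arises with standardised contrasts or unequal measurement, and the article commits to neither.

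Nor do the documents say that class differences will be read as effects of type, or that the intervention will be tailored by pattern. The pattern comparison is labelled explorative, and the intervention's stated targets are regulation and social skills.

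Two technical objections also stand. The simulations assume a single severity dimension, so they show what can happen, not what will. Parallel class profiles would also alert an analyst to severity ordering. And a rule crediting type only with what it explains beyond severity errs the other way. Take seven equicorrelated subtypes and an outcome driven by three of them. The share of explained variance that the total recovers is (3 + 18r)² / [(3 + 6r)(7 + 42r)]. At r = 0.3 this is 70.56 / 94.08 = 0.75, and at r = 0.5 it is 144 / 168 = 0.86. Most of a purely type-specific effect would be assigned to severity.

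**Conclusion.** The point holds for the latent-class patterns. The article sets patterns against cumulative risk, builds them from type and amount together, and states no severity model for comparison. As described, class differences in functioning cannot be attributed to type. When only amount matters, gaps of about 0.7 to 1.3 SD can appear while classes add about 0.003 or less to R-squared beyond a total score. These sizes rest on the assumed severity structure and effect; only N, the prevalences and the significance level come from the article.

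For threat versus deprivation the conclusion is narrower: the planned contrast can separate type from amount if both dimensions are on a common scale and equality is tested, which the article leaves open. No stated figure is overturned. This is a worthwhile improvement to the analysis, not an error that invalidates the study.

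**What to change.** In the Statistical analysis section:

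- For each main outcome and mediator, add a benchmark model with overall ACE severity: a total score or a latent general severity factor, allowing non-linearity.
- Add the LCA patterns to it and report the change in R-squared and BIC.
- Report whether class profiles cross or are merely ordered by level.
- For threat versus deprivation, enter both dimensions jointly on a common scale and test equality of their effects, including the indirect effects through emotion regulation.
- Describe pattern differences as type-specific only with this comparison shown alongside, without a fixed rule that all shared variance belongs to severity.

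The cost is a little more analysis on data already collected. The downside is that pattern effects may be reported as smaller.
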